#### 2.5.4. End of Study

Upon completion of the study, which is planned for 2022, a data monitoring board committee consisting of the research team and the coordinators of the primary care centers participating in the study will meet to distribute the satisfaction and usability surveys to the participating healthcare professionals and to collect the other primary and secondary outcome measures from the patients’ electronic health records. All these data will be made available for evaluation to an external blinded endpoint adjudication committee.

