## 2. Materials and Methods

### 2.1. Study Design

Prospective, single-blind, multicenter, randomized clinical trial. Acute COVID-19 included study patients will be randomized to one of both study arms: conventional telephone calls from healthcare professionals, periodic telemonitoring with wearable devices and mobile phone application allowing self-reporting of symptoms three times a day versus traditional telephone calls from healthcare professionals and symptom reporting application.

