### 2.2. Eligibility Criteria

To be considered for participation in the study, patients must meet all the inclusion criteria set out in this protocol without meeting any exclusion criteria (Table 1).

All patients participating in the study will receive an SMS message on their mobile phone with a link to download the healthcare app, from which they will initially electronically sign the informed consent form required to participate in the study (Supplementary Materials, File S1) and provide their contact details and home address for delivery of the Bakeey E66 smartwatch and Wellue FS20F pulse oximeter, if randomly assigned to the active group.

When patients are discharged and their home quarantine period ends, after seven or ten days depending on symptomatology, they will be able to remove the healthcare application called ‘‘Home app’’ from their mobile phone and stop wearing the monitoring devices, although their participation in the study will not end until six months after the date of the positive PCR or antigen test, when they will receive a final follow-up call from the data monitoring board to assess the primary and secondary outcome measures.

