Online platform: both the data measured by the wearable monitoring devices and the data self-reported by patients in the ‘‘Home app’’ will be uploaded to an online platform. and record that will be accessed daily by the primary care and emergency health service professionals who wish to participate in the study. Specifically, primary care professionals will be responsible for the management of moderate alarms and emergency health service professionals will be responsible for the management of severe alarms, being alerted of their existence through a computer-generated voice message. Participating healthcare professionals will have to register on the same platform and act in response to each alarm according to their clinical judgement. This will allow the research team to monitor the management of the different alarms generated throughout the study. In this way, the platform will not only serve as a clinical data registry to guide decision-making on the management of COVID-19 patients in home quarantine by both primary and specialized care, but will also serve as a repository of data that can be made available to public health agencies or even other researchers upon reasonable request (Figure 3).

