## 3. Results

As it is a protocol, this study has no results, but its publication will allow the development in the future of new lines of research based on this system for clinical decision-making, to provide personalized patient care, early detection of complications and better monitoring of the evolution of diseases. For all these reasons, we truly believe in the potential of its use for COVID-19, which could be applied in possible new variants that appear more severe, in future pandemics, in infectious diseases that require home isolation or for monitoring chronic pathologies that require a high degree of follow-up.

Ethics and Dissemination

This study follows the principles of the Declaration of Helsinki and was approved in its first version by the Drug Research Ethics Committee of the Valladolid East Health Area on 18 February 2021 (CASVE-NM-21-508). This board will be informed of any changes to this protocol and of any adverse events that may occur during the course of the research in order to consider termination of the study, if necessary.

The information obtained from the healthcare application and the wearable monitoring devices will be shared electronically with the research team for evaluation and analysis, respecting the privacy of the participants in accordance with the Organic Law 3/2018, of December 5, on Protection of Personal Data and Guarantee of Digital Rights. Participating patients may withdraw from the study at any time without affecting their usual relationship with their primary care team, although data collected up to the date of withdrawal may be used strictly for statistical analysis purposes.

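### Outcomes are collected from health records by staff with access to arm-revealing data, and blinded adjudication cannot recover a pneumonia missed at that step

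*Protocol article*

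**What the plan says.** Section 2.1 describes the trial as "Prospective, single-blind, multicenter, randomized clinical trial" and does not say there who is blinded.

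Section 2.5.4 sets up "a data monitoring board committee consisting of the research team and the coordinators of the primary care centers participating in the study". One of its tasks is "to collect the other primary and secondary outcome measures from the patients’ electronic health records". The collected data then go to an external adjudication committee, which the section states is blinded. Section 2.5.3 presents external adjudication as a measure against bias.

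Section 2.2 says that six months after the positive test, patients receive a "final follow-up call from the data monitoring board to assess the primary and secondary outcome measures". Section 2.5.3 places the final outcome call on day 30 after diagnosis and names no caller.

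On access to data that show the arm:
- Section 2.5.1, on professionals registering their response to each alarm on the platform: "This will allow the research team to monitor the management of the different alarms generated throughout the study".
- Section 3, under Ethics and Dissemination: "The information obtained from the healthcare application and the wearable monitoring devices will be shared electronically with the research team for evaluation and analysis".
- Section 2.5.1, on the centres: "primary care professionals will be responsible for the management of moderate alarms".
- Section 2.5.2 makes the devices the only difference between the arms. Section 2.6 confines the verification questions on abnormal vital signs to the active group.

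The Introduction lists pneumonia, ICU admission, invasive ventilation and death as the primary components, compared at 30 days.

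**The concern.** An outcome passes through two steps before analysis: someone finds it, and someone classifies it. The protocol blinds the second step. The first is done by a group that includes the research team, whose other duties show it which patients wear devices. No masking of the record search is stated.

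If a searcher knows the arm, the search can be more or less thorough in one arm without any intent. The committee can reject or reclassify a case that reaches it, but it cannot add one that never does. The bias could run either way. Pneumonia is the most exposed component because it depends on someone looking for it and recognising it. The hypothesis itself concerns detection of progression, so the way events are found is close to the question being asked.

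**Working it through.** **Step 1. Who collects, and what they can see.** The protocol states no figure on this point, so the check sets its sections side by side.

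| Party | Role in outcomes | Access to arm-revealing data |
|---|---|---|
| Research team | Board member; collects from records (2.5.4) | Yes: alarm management (2.5.1) and wearable data (3, Ethics and Dissemination) |
| Centre coordinators | Board member; collects from records (2.5.4) | Probable: primary care professionals handle moderate alarms (2.5.1), but coordinators' own access is not described |
| External committee | Adjudicates what was collected (2.5.3, 2.5.4) | Stated to be blinded |
| Patients | Answer the call | Know their arm, because devices are the only difference (2.5.2) |

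For the research team, knowledge of the arm follows from the text. For the coordinators it is an inference.

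**Step 2. Which components are exposed.** ICU admission, invasive ventilation and death are discrete recorded facts that leave a collector little discretion. Pneumonia leaves more.

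**Step 3. Sensitivity of the estimate.** Inputs: 250 patients per arm (Abstract; section 2.4). The event rate p is assumed, because the protocol gives none. The true effect is set to none, and m events are missed in one arm only.

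Apparent risk ratio = (250p − m) / (250p)

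| Assumed p | Expected events per arm | m = 1 | m = 2 |
|---|---|---|---|
| 2% | 5 | 4/5 = 0.80 | 3/5 = 0.60 |
| 5% | 12.5 | 11.5/12.5 = 0.92 | 10.5/12.5 = 0.84 |
| 10% | 25 | 24/25 = 0.96 | 23/25 = 0.92 |

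Low rates are plausible: the Limitations expect 80–85% of the city's population to have had two vaccine doses, and the Discussion says complications have fallen.

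**Step 4. Would a conclusion change?** For 3 against 5 events per 250:
- SE of log RR = √(1/3 − 1/250 + 1/5 − 1/250) = 0.725.
- RR 0.60, 95% CI exp(ln 0.60 ± 1.96 × 0.725) = 0.14 to 2.48; Fisher p = 0.72.

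For 23 against 25, Fisher p = 0.88. Neither comes near the 0.05 threshold of section 2.7. At the 2% rate, two missed events also means missing 2 of 5, or 40%, in one arm only, which is a severe assumption.

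**The case against.** **The trial has a blinded party.** A reader might infer that the trial is not really single-blind. The documents do not support that: the adjudication committee is external and stated to be blinded, and one blinded party is compatible with the label. What stands is that section 2.1 does not say who that party is.

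**No selection is described.** A reader might also infer that the team chooses which cases the committee sees. Section 2.5.4 makes all the collected data available and mentions no filtering. The exposure is therefore to events not found, not to events held back.

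**Silence on redaction proves little.** Rules for removing alarm and device data from adjudication files may sit in a full protocol or a charter that is not shown. Their absence from an article is not a fault, and the point does not rest on it.

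**The board is named as caller only at six months.** The primary comparison is at 30 days, and the day-30 call has no named caller. So it is not shown that the board makes the call that serves the primary outcome. This objection stands, and it leaves record collection as the core of the point.

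**A masked query does not reach the bedside.** Treating professionals see vital signs and alarms, so pneumonia may be looked for and recorded differently in the two arms before anyone opens the record. A query would reproduce that difference. This also stands and limits what the fix can achieve.

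**Conclusion.** The point holds in a limited form. The protocol assigns record-based outcome collection to a group that includes staff who can tell the arm, and it places blinding only after that step. Adjudication protects classification, not case-finding. The exposure is mainly to pneumonia and small for the other three primary components.

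The size cannot be derived from the documents. Under assumed rates of 2 to 10% and no true effect, two events missed in one arm move the apparent risk ratio to between 0.60 and 0.92, and one missed event moves it to between 0.80 and 0.96. These figures show that a low event count makes the estimate sensitive. They do not predict a bias, and they do not show that a significance conclusion would change.

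The verdict rests on the research team's stated access to alarm and wearable data, and on the coordinators' probable access. It is a cheap and worthwhile improvement, not a flaw that invalidates the trial.

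**What to change.** 1. In section 2.5.4, collect outcomes for every randomised patient by one prespecified health-record query, with the same codes, dates and sources in both arms. Run it by study ID with the arm withheld, and send all hits to the blinded committee.
2. Use the same outcome-call script in both arms.
3. In section 2.1, state that the adjudication committee is the blinded party.
4. Reconcile the timing of the final outcome call (six months in section 2.2, day 30 in section 2.5.3) and name who makes the day-30 call.
5. State as a remaining limitation that treating professionals see the alarms, so differences in how they look for and record pneumonia are not removed.

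Cost: some scripting work and changes of wording. No added assessors are needed, and patients already carry a study ID. The downside is reliance on coded records; the protocol does not say how complete or uniform the coding is, so this should be checked before the query is fixed.

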### 2.6. Patient and Public Involvement

Patients will actively participate in the study by reporting their symptoms three times a day and answering a series of verification questions when significant alterations in any of the monitored vital signs are detected (the latter only for patients in the active group). In addition, at the end of the study, both patients and participating healthcare professionals will be asked to complete a satisfaction and usability survey (SUS) to report on difficulties encountered with the Home app/online platform and areas for improvement.

### 2.7. Data Analyses Plan

A professional biostatistician has been consulted to design the data analysis plan for the study, in which descriptive analysis of all data will be provided, including means and SDs or medians for continuous variables and proportions for categorical variables. The recorded data will be processed statistically in an encrypted form.

The statistical analysis technique to be used will be the analysis of variance (ANOVA), which will allow determining the existence of significant differences between the two groups in terms of primary and secondary outcome measures. Also, the Kaplan–Meier estimator and Cox proportional hazards model will be used to establish possible predictors of mortality and/or ICU admission. The statistical software to be used will be Stata 15 and a *p*-value of <0.05 will be assumed for statistical significance.

To assess the economic impact of the intervention on the health and social system, a cost-utility analysis will be carried out to evaluate whether there are fewer hospitalizations and calls to the emergency health service in the active group than in the control group, which translates into lower costs associated with patient care. With this in mind, an acceptability curve analysis will be carried out to see whether the proposed clinical decision support system is more appropriate than the conventional primary care telephone follow-up in terms of cost-benefit ratio.

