The study will examine the differences between the active and control groups 30 days after the date of diagnosis of COVID-19, in terms of clinical progression of the disease to severe forms, defined by: progression to pneumonia, need for intensive care unit (ICU) admission, need for invasive mechanical ventilation and mortality rate. On the other hand, the secondary outcomes to be considered will be: the hospital admission rate, the average hospital stay, the occurrence of major vascular events (including acute myocardial infarction, stroke and vascular death), the economic cost of the derived care to the health system, the satisfaction of professionals and patients with the project and the usability of the technologies used in the project.

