Integration of the system modules: Regarding primary care, health professionals (nurses and doctors) will be responsible for recruiting patients. At first, the screening will be carried out on the online platform which will coincide with the first call of the conventional protocol, where it will be assessed if the patient meets the inclusion and exclusion criteria. If the patient meets the inclusion and exclusion criteria, the system will allow the baseline visit to be made, which will coincide with the first call after the patient is diagnosed with COVID-19. Data from the initial visit will be recorded, the new patient will be registered with an associated mobile phone number and an anonymous and unique ID will be provided. The online platform itself will randomly assign the patient to the case or control group. At that point, a message will be sent to activate the patient. Once the user opens the message, they will have to click on the link to download the health application called ‘‘Home app’’ where they will fill in their data, receive information about the project and data processing and sign the informed consent if they agree. In the case of the active group, a request will be sent, with the delivery address of the bracelet, to the transport company that previously arranged the shipment of the devices. Once the patient receives the bracelet, they will link the bracelet to the application and if they need support, they will receive it either via telephone call, which will be available for 14 h a day, or in the application itself. Healthcare professionals will be able to record on the web panel the registered telephone calls made according to the current protocol, the vital signs will be displayed in real-time, the responses that will be provided three times a day from patients on their perceived clinical state, and the alerts issued by the alteration of any parameter. In the event of a serious alarm, it will be received by the emergency system to provide immediate care, if required by the patient. At the end of the monitoring period, the primary health care staff will discharge the patient. In the case of the active group, the logistics will be activated to collect the devices and take them to a disinfection point. In addition, to improve the healthcare support system, a satisfaction survey and a usability survey will be carried out among patients and healthcare professionals who have participated in the study.

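### ANOVA is fixed for every between-arm comparison, but the primary outcomes are yes/no events, hospital stay has no stated value for patients never admitted, and professionals appear to belong to no arm

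*Protocol article*

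**What the plan says.** Section 2.7 (Data Analyses Plan) says "The statistical analysis technique to be used will be the analysis of variance (ANOVA", and gives its purpose: "which will allow determining the existence of significant differences between the two groups in terms of primary and secondary outcome measures". It makes no distinction by type of outcome.

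The Introduction lists the outcomes. The primary ones, at 30 days, are "progression to pneumonia, need for intensive care unit (ICU) admission, need for invasive mechanical ventilation and mortality rate". The secondary ones include "the hospital admission rate, the average hospital stay, the occurrence of major vascular events", "the economic cost of the derived care to the health system" and "the satisfaction of professionals and patients with the project and the usability of the technologies used in the project".

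On allocation, section 2.5.1 says "The online platform itself will randomly assign the patient to the case or control group". The same section has participating professionals work from one online platform holding patients' data, and section 2.5.4 has them surveyed as one body, with no arm mentioned.

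Section 2.7 names two further sets of methods. Kaplan–Meier and Cox are for predictors of mortality and/or ICU admission, not for the arm comparison. A cost-utility analysis with an acceptability curve is for cost. Categorical variables are to be described as proportions, but no test or effect measure for proportions is named.

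**The concern.** The article commits to a method, so this is not a detail left to an analysis plan. The method fits three groups of outcomes badly.

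- **Binary outcomes.** ANOVA assumes a common variance and normal errors. It yields a p-value and, at best, a symmetric interval for a difference in means. The primary result could then be reported without a risk ratio, and with an unreliable interval if events are few. Few events are plausible: patients are at home, those already progressing towards admission are excluded (Table 1), and the Limitations put two-dose vaccination in the city at 80–85%.
- **Hospital stay.** No value is given for patients who are never admitted. Read naturally, the mean is taken over those admitted, a subgroup formed after randomisation. The intervention aims to prompt earlier action, so it may change who is admitted.
- **Professionals.** A two-group test needs a grouping variable, and professionals do not seem to have one.

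**Working it through.** **Inputs.** 250 per arm (Abstract; section 2.4). Significance at p < 0.05 (section 2.7), taken as two-sided, which is an assumption. The article gives no event rates, admission rates or lengths of stay, so all of those below are assumed. It also gives no figure for this point to reproduce: its sample size rests on one-sample precision, with no planned effect or power.

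**1. The p-value for a binary outcome.** With event proportions p1 and p2 and m = 250 per arm:

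F = [m(p1 − p2)²/2] ÷ {[m·p1(1 − p1) + m·p2(1 − p2)]/498}

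Take 0 v 4 events, so p2 = 4/250 = 0.016.

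- ANOVA: numerator 250 × 0.000256/2 = 0.032; denominator 250 × 0.016 × 0.984/498 = 3.936/498 = 0.00790; F = 4.05, p = 0.045.
- Pearson: pooled proportion 4/500 = 0.008; X² = 0.000256/(0.008 × 0.992 × 2/250) = 4.03, p = 0.045.
- Fisher: p = 0.123.

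For 0 v 5 the three values are 0.025, 0.025 and 0.061. ANOVA and Pearson reached the same decision at 0.05 for every pair of counts from 0 to 59 per arm.

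Type I error by exact enumeration of two Binomial(250, p) counts:

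| Common risk | ANOVA | Pearson | Fisher |
|---|---|---|---|
| 0.5% | 0.022 | 0.022 | 0.001 |
| 1% | 0.046 | 0.046 | 0.009 |
| 2% | 0.046 | 0.046 | 0.021 |
| 5% | 0.049 | 0.049 | 0.032 |
| 10% | 0.049 | 0.049 | 0.036 |

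**2. The interval for a binary outcome.** The ANOVA 95% interval is d ± 1.965·√{[p1(1 − p1) + p2(1 − p2)]/249}. Its exact coverage of the true difference, when the active risk is half the control risk, is:

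| Control risk | Coverage | Chance of 0 v 0 | Coverage otherwise |
|---|---|---|---|
| 10% | 94.9% | negligible | 94.9% |
| 5% | 94.6% | negligible | 94.6% |
| 2% | 94.1% | under 0.1% | 94.1% |
| 1% | 91.3% | 0.99²⁵⁰ × 0.995²⁵⁰ = 2.3% | 93.4% |
| 0.5% | 83.5% | 0.995²⁵⁰ × 0.9975²⁵⁰ = 15.3% | 98.6% |
| 0.2% | 52.8% | 0.998²⁵⁰ × 0.999²⁵⁰ = 47.2% | 99.96% |

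With no event in either arm the ANOVA interval is 0 ± 0. The Newcombe interval is then ±1.5 percentage points, from the Wilson upper limit 1.96²/(250 + 1.96²) = 3.84/253.84 = 0.015. Newcombe coverage under the same halving is at least 95.8% for control risks from 0.2% to 5%.

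**3. Hospital stay.** At assumed admission rates of 2%, 5% and 10%, about 5, 12.5 and 25 patients per arm have a stay at all. As an illustration, let control have 10 admissions of 8 days, and active the same 10 plus 5 early admissions of 3 days.

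- Control: 10 × 8 = 80 bed-days; mean 80/10 = 8.0 days.
- Active: 80 + 5 × 3 = 95 bed-days; mean 95/15 = 6.3 days.

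The mean among those admitted improves by 1.7 days while hospital use rises by 15 bed-days.

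**4. Professionals.** Section 2.5.1 randomises patients. The same section gives professionals one shared platform, and section 2.5.4 surveys them together. No passage assigns a professional to an arm, so the two-group comparison in section 2.7 has no groups for their scores. This is inferred from those sections; no single sentence states it.

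**The case against.** For the primary outcomes, the ANOVA test is numerically close to the standard test for proportions. A reader might infer from 0.045 against 0.123 that ANOVA produces false significance. The figures do not support that: Pearson gives the same 0.045, ANOVA's type I error stays below 5%, and Fisher is the conservative one (0.009 at a 1% risk).

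A reader might also take the 53% and 84% coverage values as the size of the problem. They come almost wholly from trials with no event in either arm, where an analyst would hardly report an ANOVA interval. They also rest on very low risks that the article does not state, and pneumonia and admission need not be so rare. At 2–10% control risk the interval is adequate.

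The article nowhere says that stay will be compared only among those admitted. It is a condensed label whose denominator a full plan may define. The surveys are described in section 2.6 as feedback on difficulties and areas for improvement, so descriptive reporting may be what is meant for professionals. Cost has its own economic analysis besides the ANOVA sentence.

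All of this stands, and it limits the size of the point. It does not remove it: the ANOVA sentence covers every primary and secondary outcome without exception, and none of the other named methods supplies an arm comparison for the binary outcomes or for stay.

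**Conclusion.** The point holds at should-fix level. The stated method does not fit three groups of outcomes.

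- **Binary outcomes:** the loss lies in the missing effect measure and in the interval when events are sparse, not in the p-value. Under an assumed halving of risk, coverage is 94–95% at 2–10% control risk and 91% at 1%, and lower below that mainly through the zero-width interval at 0 v 0.
- **Hospital stay:** if restricted to admitted patients, the comparison is not one of randomised groups and can point the wrong way. The direction and size in this trial are unknown; the 8.0 and 6.3 days are an illustration.
- **Professionals:** the two-group test apparently cannot be run. This affects a minor secondary outcome. Patients' own satisfaction and usability scores can still be compared by arm.

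A must-fix grade would need inflated error or a clearly invalid primary test, and the documents show neither.

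**What to change.** Reword section 2.7 as follows.

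1. For each binary outcome, report the risk difference with a Newcombe or Miettinen–Nurminen 95% interval, and the risk ratio. Pre-specify the test: chi-square, with an exact test under a stated sparse-count rule, noting that Fisher's test is conservative.
2. Analyse hospital days to day 30 in all randomised patients, zero for those not admitted, with an explicit rule for deaths (for example, days alive and out of hospital). Report the difference in means with a bootstrap interval. Keep stay among those admitted as a descriptive figure.
3. Report professionals' satisfaction and usability descriptively, outside the two-group test.

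The cost is a change of wording. The outcomes are already planned; admission and discharge dates and deaths should be obtainable from the electronic health records that section 2.5.4 plans to use, though the article does not list those fields. The small downside is that the sparse-event intervals, and any exact test, are somewhat more conservative than the ANOVA results.

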### 2.3. Setting

Patients will be recruited from the two health areas of Valladolid (total target population: 560,000 habitants). The primary care centers that have been selected by the Technical Direction of Primary Care in both areas are: from Valladolid East Health Area, the centers Barrio España, Cabezón de Pisuerga, Canterac, Cigales, Circunvalación, Gamazo, Iscar, Magdalena, Medina del Campo, Olmedo, Pilarica, Portillo, Renedo de Esgueva, Rondilla, San Isidro, Santovenia and Tudela de Duero; from the Valladolid West Health, the following centers: Area Arturo Eyries, Casa del Barco, Covaresa, Delicias, Huerta del Rey, La Cistérniga, Parquesol and Plaza del Ejército. Furthermore, the Health Emergency Service of Castilla y León will participate, managing and responding to the serious alerts produced by the platform.

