#### 2.5.2. Study Arms

Patients randomly assigned to the control group will receive the conventional telephone follow-up provided by primary care to COVID-19 patients and will also be able to report their symptoms 3 times a day via the healthcare application called ‘‘Home app’’, while patients randomly assigned to the active group will also receive the Bakeey E66 smartwatch and the Wellue SFS20 pulse oximeter at home. The only difference between patients who will be assigned to the experimental group and the management group is that the latter will not be provided with portable monitoring devices.

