**Figure 2 ijerph-20-02300-f002:**
[figure not shown]
Decision tree for the generation of moderate or severe alerts based on vital signs monitored in patients allocated to the active group of the study.

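### Section 2.7 compares emergency calls between arms, but severe alarms reach the same service automatically in the active arm only, so the count is not comparable

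*Protocol article*

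**What the plan says.** Section 2.7 (Data Analyses Plan) describes a cost-utility analysis that will look at "whether there are fewer hospitalizations and calls to the emergency health service in the active group than in the control group", and adds of such a reduction: "which translates into lower costs associated with patient care". The measure, the contrast and the interpretation are thus all stated.

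The route by which the emergency service learns of a deterioration is described elsewhere:

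- Section 2.3 (Setting) gives the regional emergency service the task of "managing and responding to the serious alerts produced by the platform".
- Section 2.5.1, under the online platform, says that "emergency health service professionals will be responsible for the management of severe alarms, being alerted of their existence through a computer-generated voice message".
- Section 2.5.1, under integration of the modules, says: "In the event of a serious alarm, it will be received by the emergency system to provide immediate care". The sentence goes on to make that care conditional on the patient's need.
- The caption of Figure 2 describes the "generation of moderate or severe alerts based on vital signs monitored in patients allocated to the active group of the study".
- Section 2.5.2 (Study Arms) says of the control group that "the latter will not be provided with portable monitoring devices".

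On the records kept of alarm handling, section 2.5.1 has professionals register on the platform and act on each alarm, and comments: "This will allow the research team to monitor the management of the different alarms generated throughout the study".

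**The concern.** A measure of resource use should count the same event in the same way in both arms. Here the intervention changes how a patient's deterioration reaches the emergency service. As far as the article describes it, a control patient who worsens comes to that service by someone calling it. An active-arm patient who worsens in the same way may come to it through an alarm, with no patient call described. A count defined by the route (calls) and not by the care given (episodes) therefore depends on the arm, even if the underlying need for care is identical.

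Cost is a listed secondary outcome in the Introduction, and section 2.7 carries the analysis through to an acceptability curve comparing the system with conventional telephone follow-up. A change of route could be taken for a change in resource use. In addition, the work that the emergency service does on alarms that turn out to need no care is a cost of the system, and a count of calls does not identify it.

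**Working it through.** **Is there a figure to reproduce?** No. The article gives no expected number of emergency calls, severe alarms or false alarms. The check is therefore a comparison of the sections, followed by an illustration.

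**Step 1. The sections side by side.**

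| Element | Active arm | Control arm | Source |
|---|---|---|---|
| Telephone follow-up and symptom app | yes | yes | 2.5.2 |
| Devices | yes | no | 2.5.2 |
| Severe alerts from vital signs | yes | none described | 2.5.1, Figure 2 caption |
| Automated message to the emergency service | yes | none described | 2.5.1 |
| Calls to the emergency service | possible | possible | 2.7 |
| Unit compared | calls | calls | 2.7 |

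One route is open to both arms and the other to the active arm only. Section 2.7 names the first and is silent on the second.

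**Step 2. What the count measures.** Let E be the true number of emergency episodes in each arm, taken as equal. In the active arm, let s be the share of episodes that arrive as an alarm with no call, d the number that produce both a call and an alarm, and f the number of severe alarms that needed no care.

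- *Alarms not logged as calls:* active count = E(1 − s), control count = E, ratio = 1 − s. The active arm is understated whenever s > 0.
- *Automated messages logged as calls:* active count = E + d + f, control count = E, ratio = 1 + (d + f)/E. The active arm is overstated whenever d or f is above zero.
- *Episodes counted once, whatever the route, with alarms needing no care kept apart:* E against E, ratio = 1.00.

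If the intervention truly changes emergency use by a factor R, the first reading gives R(1 − s) and the second R + (d + f)/E, with E now the control-arm number. The true effect cannot be separated from the routing effect in either case.

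**Step 3. Illustration of the first reading.** There are 250 patients per arm (Abstract). The need for emergency contact (5%, 10% or 20%) and the share s are assumptions, since the article gives neither.

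| Assumed need | Control calls | Active, s = 25% | Active, s = 50% | Active, s = 75% |
|---|---|---|---|---|
| 5% | 250 × 0.05 = 12.5 | 9.4 | 6.25 | 3.1 |
| 10% | 250 × 0.10 = 25 | 18.75 | 12.5 | 6.25 |
| 20% | 250 × 0.20 = 50 | 37.5 | 25 | 12.5 |
| Ratio | 1 | 0.75 | 0.50 | 0.25 |

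The ratio does not depend on the assumed need; it is simply 1 − s. The second reading is not put into numbers, because nothing in the article supports a value for d or f.

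**Step 4. Does anything else in the article repair the count?** Blinded adjudication (2.5.3, 2.5.4) cannot restore contacts that the measure does not include. Section 2.5.4 takes outcome data from the electronic health records and does not mention the platform's alarm log. Hospitalizations, named in the same sentence of 2.7, do not depend on this route, but they miss emergency contacts that end without admission.

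**The case against.** The strongest reply is that the article never defines a call. The automated voice message might itself be logged as an incoming call, in which case the active arm would not be undercounted. This stands, and it rules out a tempting stronger reading: that the comparison is biased in favour of the active arm by construction. The documents support only that the count is not comparable; they do not give its direction.

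A second reply is that calls are not an outcome of this trial. The Introduction lists cost, which is broad enough to include alarm-triggered care, and section 2.7 does not say that calls are the only emergency resource to be costed or that they will be tested alone. This stands as a limit on importance. A reader might also want the probability of a falsely significant reduction in calls, but that would presuppose a separate test which the plan does not specify.

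A third reply is that the unit of count is a detail an article leaves to the full protocol or a health-economic plan. This would hold if section 2.7 were silent. It is not: it names a unit, contrasts the arms on it and attaches a cost interpretation. The point concerns what is stated.

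A fourth reply is that adding every handled alarm to patient calls would also be unfair, since alarms cannot arise in controls and some will need no care. This is correct, and the fix below is shaped accordingly.

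**Conclusion.** The point holds in a limited form. As written, section 2.7 compares the arms on a count that depends on the route of contact, while the intervention adds an automatic route in one arm only. The count understates active-arm emergency use if alarms are not logged as calls and may overstate it if they are. Neither direction nor size can be derived from the article: the ratios of 0.75 to 0.25 rest on assumed shares, equal true use and alarms that are not logged as calls. They show how the count behaves and are not an estimate of bias in this trial.

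The consequence is confined to one input of the secondary economic outcome. The primary outcome is not affected, nor is the count of hospitalizations by this route. The change is still worth making, because the interpretation of fewer calls as lower cost is written into the plan and the change is small.

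**What to change.** In section 2.7, replace calls by emergency-service episodes that led to a service response (for example telephone management, dispatch or attendance). Count them once per event and in the same way in both arms, whatever the route of activation. An event that produces both a call and an alarm is then one episode.

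Report the episodes by route, patient-initiated or alarm-triggered. Cost the handling of severe alarms that needed no care, including false alarms, separately as a cost of the intervention, and do not add them to the episode count.

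The responses to alarms are already to be registered on the platform (section 2.5.1), so that source should be named in section 2.7. This concerns measurement only and changes nothing in how alarms are handled. The cost is a little more analysis work, and the active arm's emergency-use or cost figure may become less favourable.
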